#### Secondary Analyses

Total set goals and specific lifestyle area goals will be reported descriptively. The changes of lifestyle within the goal setting group will be reported in absolute difference at end of intervention. The dose-response association between goals and change of lifestyle will be analyzed by multivariable linear regression model, and potential confounders will be adjusted. The change in self-efficacy and self-control scores will be reported in absolute difference at the end of the intervention. The association between the use of BAM and increased feelings of self-efficacy or self-control will be analyzed by multivariate analysis.

Analysis will be performed per protocol. The dropout in this pragmatic field study is likely to be high but can be considered a separate outcome for the implementation and feasibility of these types of intervention. As such, it represents valuable data about the quasi-experimental study design.

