After a participant has decided which instructions and tips to use, the goal gets transferred to the short-term monitoring system (STMS). Here, participants can monitor their own behavior on a day-to-day basis. Inputting their behavior in the STMS, the system automatically graphs a quick overview of how well a participant is doing for that goal on a week-to-week basis. After a month, the STMS asks the participant to what extent the goal is accomplished on their own original GAS scale. For any score specific to that goal, the BAM gives tailored feedback. If a score of -2 or -1 is obtained, the goal is deleted from the participant’s profile and encouragement to try again is given. However, if a score of 0, 1, or 2 is obtained, the goal gets transferred to the long-term monitoring system (LTMS). In the LTMS, a participant gets monthly follow-up questions to monitor if they still are maintaining their initial level of behavior change. With every monthly question that gets answered, the participant is given tailored feedback to acknowledge their success or motivate the participant to maintain their initial behavior change. Multiple goals can be graphed over time giving a personal overview of all acquired and maintained behavior change goals. If multiple goals are set on the same subject, new goals will overwrite old goals so that only the most up-to-date information is shown. Because the BAM does not dictate how many a goals a participant sets and in what order they do this, it implicitly provides the participant with a conceptual choice between simultaneous or sequential goal setting, giving every participant the option to work at their own pace and preference [50-52].

In order not to overload the participant with questionnaires immediately after registering, the personality questionnaires become available to the participant 7 days after registration. These are the Dutch General Self-Efficacy Scale [53], lifestyle factor specific self-efficacy questions [54], the Positive Affect Negative Affect Scale [55], and the Self-Control Scale [56]. These questionnaires are administered to perform secondary analyses to check if the BAM is more effective in certain personality types. No feedback on the personality questionnaires is provided for the participants.

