After all baseline data are collected, the tailored knowledge databases, the buddy system, healthy recipes, and blogs on health behavior and cognitive aging become available. The buddy system is a built-in control mechanism the BAM uses to ensure goal safety. A subset of goals that are suitable for this purpose are anonymously sent to another BAM user to be judged by a BAM buddy on its feasibility and safety. A buddy can judge a goal to be “ambitious”, “not ambitious enough”, “just right”, or in the case of losing weight, “this seems unhealthy”. This gives the goal-setter an opportunity to get instant feedback on the feasibility of their goal. Also, it gives the buddy a “look behind the scenes” that may provide feedback on their own goal-setting behavior, as the exact same situation for somebody else may be perceived as harmful whereas this same goal would be deemed applicable to the participant themselves. At the same time that the buddy system becomes available, participants also get access to the knowledge databases that contain up-to-date information on healthy living and the relationship between the different behaviors and brain health. Last, participants get access to weekly blogs on lifestyle, research and brain aging, and healthy recipes. After 365 and 730 days upon completion of the baseline measurement, they will be recruited for 1-year and 2-year follow-up measurements.

No reasons for discontinuation of the study of a participant by the research team have been specified. There is no disease load that can be exacerbated by participating in the BAM nor is there any medication prescribed that could have negative health consequences. Participants are provided with the option of unsubscribing to the study at any given time in their personal profile space. When a participant decides to leave the program, a short questionnaire is automatically presented to collect data on the reason for unsubscribing and to inquire if the participant may be approached to partake in the 1-year and 2-year measurement, regardless of subscription status. All of this is voluntary and participants can always choose to skip this questionnaire.

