### Sample Size

We aim for a group size of 200 to find a 15% reduction on the risk factors (power calculation based on alpha <.05; power of 0.8; two-tailed; n=166; ±20% dropout).

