### Data Collection Methods

Data collection in the BAM is completely automated through its website. Therefore training of personnel is irrelevant. All data collection forms will be equal for each new participant who subscribes to the program. For collection of the descriptive lifestyle data, questionnaires have been used that accurately represent the relevant health norm or health behavior (full lifestyle questionnaires can be found in Multimedia Appendix 2). For measuring cognitive functioning, the BAM program uses a validated online self-monitor for cognitive functioning, specifically developed for use in the BAM, called the BAM-COG [47]. We have deliberately chosen to keep the baseline assessment as concise as possible. Creating a complete overview of a participant’s lifestyle can be a tedious task and with high risk of early dropout in eHealth interventions, the BAM’s lifestyle assessment is meant to give a fast and easy overview of a participant’s compliance to health norms, not a detailed description of all facets that make up healthy living.

The BAM intervention has multiple built-in mechanisms aimed at increasing retention to protocol. As described in the intervention section of this protocol, we will use blogs and recipes in the intervention to keep participants’ focus on the program, as well as the deployment of the adjustable reminder system and the flexible use of newsletters. When the program has been online for 365 and 730 days, special newsletters will be sent out to all active participants reminding them of their annual follow-up measurement that becomes available on their personal dashboard.

Participants who want to exit the study can do so at any time. They can unsubscribe from their personal profile page using the unsubscribe instructions. Once this process is initiated by the participant, a short questionnaire will be used to identify the reason for dropout. Also, the BAM will ask the participant if they are still willing to be reminded of the annual measurements. In this case, they would not actively participate in goal setting and behavior monitoring but would be willing to come back and provide the program with follow-up data.

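### The only stated analysis principle is an undefined per-protocol analysis, in an uncontrolled study that expects high dropout and plans follow-up of unsubscribers

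*Protocol article*

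**What the plan says.** Under Statistical Analyses, the Secondary Analyses subsection states "Analysis will be performed per protocol. The dropout in this pragmatic field study is likely to be high" and goes on to treat that dropout as an outcome in its own right. The wording is general. The Intervention Effects subsection, which covers the primary analyses, names no other population and says those analyses are unadjusted. Per protocol is not defined anywhere in the article.

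Other sections bear on what the phrase could mean:

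- **Intervention, on use:** "Because the BAM does not dictate how many a goals a participant sets", the order and pace of goals are also left to the participant. No minimum use is prescribed.
- **Intervention, on leaving:** a short exit questionnaire, which may be skipped, is used to "inquire if the participant may be approached to partake in the 1-year and 2-year measurement, regardless of subscription status".
- **Data Collection Methods:** unsubscribers who agree would no longer set goals or monitor behaviour but "would be willing to come back and provide the program with follow-up data".
- **Sequence Generation, Allocation Concealment Mechanism, Implementation, and Blinding:** there is no control group.
- **Sample Size:** a target of 200, with "power calculation based on alpha <.05; power of 0.8; two-tailed; n=166; ±20% dropout".
- **Research Questions and Outcome Measures:** primary question 1 is whether lifestyle change relates to cognitive aging. Questions 2 and 3 are whether the programme changes lifestyle overall and by area.

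**The concern.** A per-protocol set is chosen on behaviour after baseline. Here that behaviour is continued engagement with a voluntary self-help programme, which is plausibly linked to whether lifestyle is improving. The article's Discussion itself treats adherence as often decisive in such programmes.

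In a randomised trial a second arm would at least give a comparison. Here the estimate is a before-after change in one group, unadjusted in the primary analysis, so nothing in the design offsets the selection. Reporting dropout as an outcome of its own describes attrition but does not correct the change estimates.

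At stake is whether the lifestyle and cognitive change results speak for the people who registered, or only for those who stayed engaged.

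**Working it through.** **1. The passages side by side.** The article plans follow-up scores from people who have stopped using the programme, and also says analysis is per protocol. The usual meaning of per protocol excludes people who stopped the intervention, which would leave those scores unused. A looser meaning (anyone with follow-up data) keeps them but makes the analysis one of completers, still selected by who returns. No use threshold exists to decide between the two, so any definition made later would be a choice based on post-baseline engagement.

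**2. The plan's own figures.** 166 × 1.20 = 199.2, rounded up to 200, reproduces the target. Dividing instead gives 166 / 0.80 = 207.5, or 208. The base of 166 cannot be reproduced, because no baseline rate, SD or test is given. If it came from a paired normal test (assumption), the detectable standardised change is (1.960 + 0.842) / √166 = 0.217 SD. A 20% loss gives the 80% retention case below. No figure accompanies the statement that dropout is likely to be high, so 50% and 30% retention are assumptions.

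**3. Illustration of selection.** Assume true mean change 0 with SD 1 and 200 enrolled. The fraction p who stay are those highest on a normal variable that correlates ρ with change. The documents give no value for ρ.

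- Stayers' mean change: b = ρλ, where λ = φ(k)/p and k = Φ⁻¹(1 − p).
- λ = 0.2800/0.8 = 0.350; 0.3989/0.5 = 0.798; 0.3477/0.3 = 1.159.
- Stayers' SD: s = √(1 − ρ²λ(λ − k)), between 0.966 and 1 for the cases below.
- Chance that a two-sided 5% test rejects: Φ(x − 1.96) + Φ(−x − 1.96), where x = (b/s)√(200p).

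| ρ | b at 80% (n=160) | b at 50% (n=100) | b at 30% (n=60) | Rejection at 80 / 50 / 30% |
|---|---|---|---|---|
| 0 | 0 | 0 | 0 | 0.05 / 0.05 / 0.05 |
| 0.1 | +0.035 | +0.080 | +0.116 | 0.073 / 0.126 / 0.147 |
| 0.2 | +0.070 | +0.160 | +0.232 | 0.145 / 0.366 / 0.445 |
| 0.3 | +0.105 | +0.239 | +0.348 | 0.273 / 0.693 / 0.796 |

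A negative ρ gives the same sizes with the sign reversed. At ρ = 0.2 and 30% retention the artefact (0.232 SD) exceeds the 0.217 SD from step 2.

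**4. What an all-available-data analysis would and would not repair.** It brings in scores from unsubscribers who return and from people seen at 12 but not 24 months. How many that would be is unknown. For people who never return, a likelihood-based model assumes missing at random. In step 3, staying depends on the change itself. If change is unrelated to baseline, a model with baseline and one follow-up leaves the step 3 bias for never-returners as it is.

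Setting non-returners to zero change multiplies the bias by p. At ρ = 0.3 this gives 0.8 × 0.105 = 0.084, 0.5 × 0.239 = 0.120 and 0.3 × 0.348 = 0.104 SD. To recover the true zero, non-returners' mean change would have to be −pb/(1 − p): −0.42, −0.24 and −0.15 SD. A sensitivity analysis therefore has to allow for values worse than no change.

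**5. The association in primary question 1.** If the true lifestyle-cognition correlation is 0.20 (assumption) and retention depends only on lifestyle change, stayers' correlation is 0.20s / √(1 − 0.04 + 0.04s²). At ρ = 0.3 this is 0.196, 0.194 and 0.194 for 80%, 50% and 30% retention: slight attenuation. Selection on both variables could behave differently and was not worked out.

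**The case against.** **An article condenses its plan.** That would excuse a missing definition on its own. It does not excuse the stated rule: an analysis plan would have to contradict the sentence to repair it. The sentence sits under Secondary Analyses, but its wording is general and the primary analyses are given no other population.

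**Exclusion of unsubscribers is not stated.** A reader might infer that the plan discards everyone who unsubscribes. The documents do not say so. Since no minimum use is prescribed, an unsubscriber who returns both measurements might even count as per protocol. Exclusion is the ordinary reading, no more. Nor are unsubscribers told to return: they are asked whether they may be approached and can skip the question, so their data would be partial. This objection stands and limits the claim.

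**The figures measure attrition, not the rule.** The step 3 model treats everyone who is not a stayer alike. It does not separate people with data whom a per-protocol rule would drop from people who never return. Only the first group is due to the criticised sentence, and its size is unknown. This stands in full.

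**The direction is not established.** The Intervention section describes the programme as a possible gateway to other platforms, so some who leave may be doing well elsewhere. Upward bias is the more plausible direction, but the documents give no link between staying and success.

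**The main outcome is an association.** The Abstract names the relationship between lifestyle change and cognitive aging as the main outcome. The figures for mean change do not carry over to it, and the one case worked out shows slight attenuation rather than inflation.

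**Conclusion.** The defect holds. An undefined per-protocol analysis is the only stated principle in a single-group pre-post study that expects high dropout, sets no minimum use and plans follow-up of people who have left. On its ordinary reading it bases the lifestyle and cognitive change estimates on self-selected stayers and leaves planned data unused.

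The likely consequence is an overstated mean improvement for primary questions 2 and 3. Its size is not in the documents. Under the assumed normal selection model with correlations of 0.1 to 0.3, it ranges from about 0.04 SD (80% retained) to 0.35 SD (30% retained), for all loss of follow-up together.

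Three stronger readings are tempting and not supported: that unsubscribers are certainly excluded, that the results certainly overstate improvement, and that the lifestyle-cognition association is inflated. Confidence is high in the defect, and lower in the direction and size of its effect.

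**What to change.** Replace the per-protocol sentence with the following:

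1. **Primary analysis set:** all participants who meet the age criterion and completed baseline, whatever their later use or subscription status.
2. **Data used:** every available 12- and 24-month score, including those from unsubscribers, for example in a likelihood-based repeated-measures model. State that this assumes missing at random.
3. **Sensitivity analysis for non-random dropout:** set non-returners to zero change, or apply a delta shift over a stated range that includes values worse than no change. The model in item 2 does not remove bias when staying depends on the change itself.
4. **Per protocol:** keep it as supportive only, with a definition fixed before the follow-up data are examined.

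Reporting dropout as a feasibility outcome can stay as it is. The cost is revised wording and a small amount of extra analysis, with no new data collection. The estimates will probably look less favourable.

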### Data Monitoring

There will be no data monitoring committee for this intervention, as no adverse events are expected. No interim analysis will be performed for the same reason. No significant harm to the participants is to be expected for the BAM intervention program. If anything would occur, participants can contact the research team through the contact form on the website. Standard data monitoring procedures for the scientific Geriatric Medicine department at the Radboudumc apply.

### Auditing

No auditing is planned specifically aimed at the BAM study. However, the BAM is part of the scientific branch of the Geriatric Department of the Radboudumc and therefore can be routinely audited internally.

### Research Ethics Approval and Protocol Amendments

The program is largely implemented in medium-to-large corporations that transparently implement the program as part of their health policy. From individual participants, an online informed consent form for their participation in scientific analysis is obtained during registration for the program. This study was deemed exempt from formal ethical evaluation by the local medical ethics committee (region Arnhem-Nijmegen, registration number: 2014-1268). Protocol amendments will be submitted, if necessary.

### Informed Consent

Due to the online nature of this study, no personal informed consent can be obtained from participants. However, we do use an online informed consent form to make sure that participants are aware of their participation in scientific research. Therefore an extra step has been added to the registration process. After email verification, before a participant can start the program, a screen appears with an informed consent form. If informed consent is not provided by ticking the correct box, participation in the program cannot continue. See Multimedia Appendix 1 for a complete translation of the information provided and accompanying informed consent form.

### Confidentiality

All information stored in online databases is random-password protected. Also, all our websites use state-of-the-art SSL-security certificates to ensure maximum safety of participants’ confidential information. MySQL data that contain names are stored in different tables as study results. Exported data from the MySQL online databases will be downloaded to local password-protected hard drives for analysis. Also, when databases are saved on local hard drives, these databases will be stored anonymously, using only anonymous personal identifier codes for all participants. No print records will be kept at any point during the study. Participants’ study information will not be released outside of the study without the documented permission of the participant.

### Access to Data

Only principal investigators, post-docs, and PhD students involved in the study will have access to the full raw dataset. Other researchers interested in using the BAM dataset will get access to a cleaned dataset. Human resources departments of recruited companies will, at no point, get access to any form of dataset. They will receive anonymous overall group results of data analysis.

### Ancillary and Post Trial Care

Participants can always contact the research team by phone or email with any questions they may have. Also, the BAM will remain available to them after the study closes since the BAM is part of a national Quick Results grant aimed at providing fully functional end products at the end of the study period.

### Dissemination Policy

Study results, regardless of their direction of outcome, will be published in high standard, peer-reviewed scientific journals. Study publications will be written on primary and secondary outcomes and subgroup analysis. Researchers and health care professionals will be updated on study results during national and international conferences and workshops and with targeted tailored publications in relevant professional magazines.

Participants who unsubscribe to the program are given the option to stay updated on study results when these become publicly available in the form of a summary of the research report or PhD thesis. Participants who stay in the program until the study period closes will be approached by email to probe their interest in study results. Furthermore, study results will be made available to the general public via a press release issued by the Radboudumc after publication of the primary outcomes. No publication restrictions apply, and no ghost- or professional medical writers are involved in the study.

## Results

Study results are expected to be published early in 2016.

## Discussion

### Principal Considerations

To our knowledge, this is the first large study that aims at health behavior gains with a cognitive motivation and outcome measure in the general population. Furthermore, the BAM is one of the first studies launched in an era when almost everybody has an Internet connection. As such it can serve as a proxy for the feasibility of these types of interventions when specifically launched in the general population.

Enhancing the BAM with state-of-the-art, scientifically validated applied games gives the unique advantage of being capable of measuring cognitive functioning while maintaining all the advantages such as reach and low cost that are associated with eHealth studies. The use of online applied games from the safety and comfort of one’s home gives us another major advantage. It also provides a motivational edge, since playing games is considered more appealing than participating in standard neuropsychological testing. We decided to use self-reporting measures for the BAM instead of more objective clinical measures (eg, blood pressure, cholesterol) because use of these measures in a general community dwelling research population is either not feasible or expensive and a big logistic challenge. Moreover, using a participant’s self-reported input closely matches the participant’s perception of their own behavior. Therefore, the goals a participant sets are more likely to be perceived as personally relevant and the participant will feel ownership over the goal and behavior change that needs to be achieved. Combined, we feel this increases the odds of successful implementation of the BAM.

We chose a quasi-experimental design as it seems more appropriate for a field setting in which it is highly impractical to initiate a randomized controlled trial, and blinding participants to the type of eHealth intervention they are receiving is practically impossible [65]. Theoretically, it was preferable to use a step-wedge cluster-randomized controlled design, but this was not feasible with the current 2-year intervention period. Since recruitment of companies is not guaranteed, cluster randomizing from the start is also difficult, especially since organizations are not very likely to see the incentive of participating as a control group. There is also a pragmatic side to the choice of the population. There is substantial theoretical background to select participants aged 40 and older [42], since in this part of the working population cognitive decline can already be measured, and they are more likely to be triggered by a dementia prevention program. People under 40 are less likely to be triggered by cognitive decline or even dementia prevention, as it is a disease associated with old age and only in later years a relevant threat to their health. Nonetheless, the BAM will allow participants under 40 to subscribe. However, lifestyle advice will be tailored to age cohorts starting at age 40.

Last, the use of a multimodal lifestyle perspective is a strength, as it gives potential participants a more integral overview of lifestyle. Providing a more comprehensive lifestyle overview allows the participant to prioritize one type of change over another and take a holistic approach to their own lifestyle. Also, benefits from changing one behavior may transfer to improved outcomes on another behavior that would go unnoticed in single modal interventions. Since the BAM is an eHealth intervention, tailoring to the needs of the participant is cheap after initial development costs have been incurred. Targeting personally relevant lifestyle factors after providing a more general overview should improve program adherence because the participant becomes aware of why they are working on a certain risk factor. This is important as adherence is often the crucial factor in lifestyle improvement programs.

